### Recruitment {15}

At least 328 patients will be recruited from the Seventh Affiliated Hospital of Sun Yat-sen University through the publication and distribution of text messages, phone calls, and advertisements containing information of the study. Physicians screen potential patients for inclusion and exclusion criteria and register information in the subject registration form. One study investigator checked patients' eligibility for inclusion before randomization.

## Assignment of interventions: allocation

### Sequence generation {16a}

A random number table will be generated using SAS software and assigned according to a random number in a 1:1 ratio by an appointed investigator.

### Concealment mechanism {16b}

The random grouping results (Group A or Group B) corresponding to the enrolment number of the participants will be placed inside the opaque, sealed envelopes.

### Implementation {16c}

After the eligibility of the participants is confirmed and informed consent is obtained, a trial number will be assigned only after all inclusion and exclusion criteria have been met. Participants will be randomly assigned to the trial (see flowchart in Fig. 1).

**Fig. 1 Fig1:**
[figure not shown]
Flowchart of the study

## Assignment of interventions: blinding

### Who will be blinded {17a}

Given the nature of the intervention, it is not possible to blind the physicians, nurses, and patients. One critical care physician who is not aware of the clinical research and intervention will collect data on clinical and vital signs. In addition, a team of experts consisting of one ultrasonographer, one radiologist, and one intensivist, have been established to interpret the ultrasound and chest radiograph results. Each member of the team of experts is at least an attending physician and unaware of the patient information.

### Procedure for unblinding if needed {17b}

Unblinding will only be allowed under emergencies such as the incidence of serious adverse effects.

## Data collection and management

### Plans for assessment and collection of outcomes {18a}

Baseline variables such as age, sex, body mass index, and chronic comorbidities will be collected on admission by physicians. Data related to surgical conditions like planned surgical procedure, ARISCAT score, mechanical ventilation will be acquired from the electronic medical record. Laboratory tests will be conducted at the laboratory. Chest X-ray and ultrasound examination will be performed by a radiologist and an ultrasonographer, respectively. All relevant data will be stored in the research folder, accessible only to the study group.

### Plans to promote participant retention and complete follow-up {18b}

At each postoperative visit and breathing guide, the study staff will answer participants’ questions, and recommend measures to promote their recovery. Biweekly telephone calls will be made to check responses for completion of their follow-up.

### Data management {19}

All data will be recorded in the paper case report form (CRF), and.subsequently entered into an electronic database. Data are managed by a designated investigator. Any study folder reflecting personal information of the subjects will be stored in a locked room.

### Confidentiality {27}

The research records and data are identified by the unique code corresponding to names and other personal information of the subjects. Relevant study investigators are only permitted to get access to these information. Data entry into databases, public exchanges, and publication of research results will use numbers instead of names and other personal information.

### Plans for collection, laboratory evaluation, and storage of biological specimens for genetic or molecular analysis in this trial/future use {33}

There will be no biological specimens collected.

## Statistical methods

### Statistical methods for primary and secondary outcomes {20a}

The Shapiro–Wilk test will be used to test whether continuous variables are normally distributed. Normal distribution will be expressed as mean ± standard deviation, and the independent samples t-test will be used to compare between groups. Non-normally distributed continuous variables will be expressed as the median (or interquartile range) using the Mann–Whitney *U* test comparison. Enumeration data will be expressed as the number of cases and percentages, and comparisons between groups will be performed using the chi-squared test. Survival time will be analysed using Kaplan–Meier survival analysis, and comparisons between groups will be performed using the log-rank test. SPSS version 22.0 software (IBM Corp., Armonk, NY, USA) was used for all analyses.

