### Objectives {7}

Primary objective: To reduce the incidence of PPCs within 7 days of surgery compared with routine use of COT and apply these findings to clinical practice.

Secondary objective: To investigate whether HFNC combined with respiratory training can improve postoperative outcomes of patients, such as reducing 28-day mortality, 1-year all-cause mortality, reintubation rates, and length of hospital stay after major upper abdominal surgery.

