#### Secondary outcome

Secondary outcomes include the following: incidence of PPCs during hospitalization, length of hospital stay, 28-day mortality, NIV or reintubation rates, incidence of surgical complications (surgical site bleeding, infection, wound infection, anastomotic leakage, and surgical reintervention), and all-cause mortality within 1 year.

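### The default test for length of stay does not separate in-hospital death from discharge alive, so an early death could rank as a good outcome

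*Protocol article*

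**What the plan says.** The Outcomes section of the protocol article lists "length of hospital stay, 28-day mortality, NIV or reintubation rates" among the secondary outcomes, with mortality as a separate item. The other listed outcomes are incidences, rates or mortality, so stay is the only continuous one.

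The secondary objective expects benefit on both fronts: "such as reducing 28-day mortality, 1-year all-cause mortality, reintubation rates, and length of hospital stay".

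The section on statistical methods for primary and secondary outcomes has a single rule for continuous variables. A Shapiro–Wilk "test will be used to test whether continuous variables are normally distributed". If they are, "the independent samples t-test will be used to compare between groups". Otherwise, "Non-normally distributed continuous variables will be expressed as the median" and compared by the Mann–Whitney test. Kaplan–Meier and log-rank methods are named for survival time only. The section names neither length of stay nor the handling of patients who die in hospital.

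**The concern.** A hospital stay ends in one of two ways, and a short stay is good only if it ends in discharge. A rank test on observed stays cannot tell the two apart: a patient who dies on day 4 scores better than one who goes home on day 10. If the intervention prevents early deaths, the survivors it adds to Group A contribute longer stays in place of short ones. Success on mortality then counts against success on length of stay. A real shortening could be missed, or an arm with more early deaths could be flattered on this outcome. Reporting mortality separately shows the deaths but does not correct the length-of-stay test.

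**Working it through.** **Does the rule reach length of stay?** Stay is the only continuous outcome listed, so the rule for continuous outcomes either governs it or governs no listed outcome.

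**Do other provisions remove the deaths?** Not reliably.
- The final analysis is limited to patients with more than 75% adherence. The minimum interventions last 48 h (oxygen therapy) and 3 days (training), so a patient who dies on day 4 or later can be fully adherent and stays in.
- Multiple imputation applies to missing data. A patient who died has no missing day of live discharge.
- Data from a withdrawn patient are kept up to withdrawal. Applied to a death, this gives a stay cut off at death.

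**How large could the effect be?** The plan has no figure for length of stay to reproduce, so all inputs except the arm size are assumptions:
- 164 per arm, as stated under Sample size (set for the primary outcome; taken as given).
- Survivors' stay log-normal, median 10 days in Group B, log-SD 0.5; median 14% shorter in Group A (8.6 days).
- Deaths spread over days 2–8.
- Mann–Whitney test at two-sided 0.05, counting significant results in favour of Group A.

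One mortality pair can be tied loosely to the article. Its Background cites 46,200 deaths per nearly one million pulmonary complications, which is 46,200 / 1,000,000 = 4.62%. Applied to the planning rates (40%, and 15 points lower at 25%):
- Group B: 0.40 × 4.62% = 1.8%, or 164 × 0.018 ≈ 3 deaths
- Group A: 0.25 × 4.62% = 1.2%, or 164 × 0.012 ≈ 2 deaths

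This is an extrapolation. The cited figure is a US national estimate with no timing, and deaths without a pulmonary complication are left out. The other pairs are illustrative.

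Simulated power (ranges are across repeated runs):

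| Mortality, B vs A | Observed stays, deaths on days 2–8 | Observed stays, deaths on days 5–28 |
|---|---|---|
| none | about 76% | about 76% |
| 1.8% vs 1.2% | 71–72% | 75–77% |
| 3% vs 1% | 64–65% | 78–79% |
| 5% vs 2% | 58–60% | 79–80% |

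The fair benchmark for masking is the no-deaths row. Early deaths cost about 76 − 72 = 4 points at 1.8% vs 1.2%, and about 76 − 60 = 16 points at 5% vs 2%. With deaths on days 5–28 there is no material loss.

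**Second set of assumptions.** 148 evaluable per arm (164 × 0.9), median 12 days, log-SD 0.5, 15% shorter stay and mortality halved in Group A. Power without deaths was about 77–78%.

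| Group B mortality | Deaths at median day 5 | Median day 12 | Median day 20 |
|---|---|---|---|
| 2% | 72% | 77% | 78% |
| 5% | 66% | 74% | 79% |
| 10% | 49% | 70% | 79% |

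The pattern is the same: the loss is large only when deaths are both early and fairly common.

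**What worst-rank scoring adds.** In the first scenario, ranking deaths worst gives about 83% power at 5% vs 2%, which is above the no-deaths 76%. Part of that gain is the mortality difference itself. With no true difference in stay at 5% vs 2%, the worst-rank test favours Group A in about 6–7% of runs, against 2.5% nominal.

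**The case against.** A reader might infer that the plan counts in-hospital deaths as short stays. It does not say so. The quoted words concern normality testing, and the section mentions neither stay nor death. How deaths enter a secondary outcome is also a detail that an analysis plan not shown here may settle. This stands as a limit on the wording. It does not remove the point: the article states a method for continuous outcomes, and that method, applied to the one such outcome, does not suit it.

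The size depends on unsourced assumptions, above all on when deaths occur. This stands in full. The eligibility criteria exclude patients not extubated within 24 h and those with haemodynamic instability, two groups in which very early deaths might be expected. Late deaths remove the masking.

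A reader might also fault the normality pretest. That changes no result here: a skewed stay that fails the pretest goes to the Mann–Whitney test, which is one of the suitable tests anyway.

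Finally, a worst-rank analysis has its own cost, because it partly tests mortality. This too stands, so the gain from worst-rank scoring should not be read as the size of the problem.

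**Conclusion.** The point holds in a limited form. By default, length of stay is compared without separating death from live discharge. If observed stays are used and deaths come before usual discharge, the comparison works against the arm with fewer deaths. On the assumptions above, the loss is about 4 points of power at 1.8% vs 1.2% mortality and about 16 points at 5% vs 2%, and it vanishes if deaths come around or after usual discharge. In-hospital mortality, its timing and the distribution of stay are all assumed, since the documents give none of them. The primary outcome is unaffected, and the priority is low.

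**What to change.** Add one or two sentences to the statistical methods, before outcomes by arm are examined. State that in-hospital death is not a discharge, and name one analysis for length of stay:
- time to discharge alive, with death as a competing event; or
- the Mann–Whitney test, with in-hospital deaths ranked worse than the longest stay.

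Report in-hospital deaths by arm and the survivors' median and interquartile range alongside.

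No new data are needed: the participant timeline (Table 1) already records vital status at the end of hospitalisation. The cost is one of interpretation. The result then combines stay and death and must be labelled so.

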### Outcomes {12}

#### Primary outcome

The primary outcome is the incidence of PPCs within 7 days after surgery. This includes respiratory infections, bronchospasm, aspiration lung injury, pneumonia, atelectasis, pleural exudation, pneumothorax, and acute respiratory failure, according to the EPCO definitions [24]. Each diagnostic criterion is available in the Additional file.

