### Methods for additional analyses (e.g., subgroup analyses) {20b}

The treatment effect will be analysed according to the following pre-specified subgroups: (1) open surgery and laparoscopic surgery and (2) patients at high risk for PPCs (ARISCAT score ≥ 45).

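### The primary outcome is compared with an unadjusted chi-squared test although ARISCAT score and surgical approach should be known at randomisation: a valid test, but efficiency is given away

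*Protocol article*

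**What the plan says.** The endpoint is binary: "The primary outcome is the incidence of PPCs within 7 days after surgery" (Primary outcome). The section on statistical methods {20a} sends all categorical data to one test: "comparisons between groups will be performed using the chi-squared test". It names no adjusted model, and it names SPSS 22.0 for all analyses.

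The section on assessment and collection of outcomes {18a} lists the prognostic data: "Data related to surgical conditions like planned surgical procedure, ARISCAT score, mechanical ventilation will be acquired from the electronic medical record". The section on additional analyses {20b} uses two such factors, for subgroups only: "1) open surgery and laparoscopic surgery and (2) patients at high risk for PPCs (ARISCAT score ≥ 45".

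On allocation, Sequence generation {16a} says "A random number table will be generated using SAS software", with a 1:1 ratio. It mentions neither strata nor blocks. The Methods paragraph of the abstract places randomisation after extubation.

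**The concern.** The protocol treats ARISCAT and surgical approach as important enough to define subgroups, but leaves both out of the main comparison. The population looks mixed in risk. The inclusion criteria admit abdominal surgery of at least 2 hours with no risk threshold, the consent section provides for emergency cases, and the Introduction cites PPC incidences from 6% to 80%. With mixed baseline risk, adjusting for prognostic factors can sharpen the treatment comparison without any extra patients.

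Two things are at stake. One is power, in a trial whose sample size already gives less than the 90% it states. The other is the reading of the result. If no stratification was used and the arms differ by chance in ARISCAT or approach, there will be pressure to adjust after the fact. Adjustment chosen after the data are seen carries much less weight than adjustment fixed in advance.

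**Working it through.** **Inputs.** From Sample size {14}: control risk 40%; 15% lower in Group A, read as absolute, so 25%; alpha 0.025, sidedness not stated; beta 0.1; loss 10%; 164 per arm. Evaluable per arm: 164 × 0.9 = 147.6, about 148.

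**Step 1. Reproduce the plan's figure.** With p̄ = 0.325:

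n = [z_α √(2p̄(1−p̄)) + z_β √(p₁(1−p₁) + p₂(1−p₂))]² / (p₁−p₂)²

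The two roots are √0.43875 = 0.6624 and √0.4275 = 0.6538.

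- One-sided 0.025: (1.960 × 0.6624 + 1.2816 × 0.6538)² / 0.0225 = 203, or 226 after dividing by 0.9.
- Two-sided 0.025: (2.2414 × 0.6624 + 1.2816 × 0.6538)² / 0.0225 = 240, or 267 with loss.

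The stated 164 is not reproduced. That is a separate problem, but it sets the starting point here.

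**Step 2. Power of the stated test.** Power = Φ[(0.15√n − z_α × 0.6624) / 0.6538].

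- n = 148, one-sided 0.025: Φ[(1.8248 − 1.2983) / 0.6538] = Φ(0.805) = 79.0%.
- n = 148, two-sided 0.025: Φ[(1.8248 − 1.4847) / 0.6538] = Φ(0.520) = 69.9%.
- n = 164: 83.0% and 74.8% respectively.

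**Step 3. Gain from adjustment.** The article gives no prognostic strength, so it has to be assumed. Simulation of 4,000 trials per row compared the chi-squared test with logistic regression on arm, high ARISCAT and open surgery. Marginal risks were 40% and 25%, each factor was independent with 40% prevalence, and the test was two-sided 0.05 (the same critical value as one-sided 0.025). At 148 per arm:

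| Assumed odds ratios (high ARISCAT, open) | Unadjusted | Adjusted | Gain, points |
|---|---|---|---|
| 1, 1 | 79.9% | 79.6% | −0.3 |
| 2, 1.5 | 79.0% | 80.1% | 1.1 |
| 3, 2 | 78.3% | 81.9% | 3.6 |
| 5, 2 | 79.3% | 84.6% | 5.3 |
| 8, 2 | 79.9% | 87.9% | 8.0 |

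The simulation error of one power figure is about √(0.8 × 0.2 / 4000) = 0.6 points, so the first row shows no real loss. A separate simulation with one continuous score (1,500 trials per scenario) gave 79.3% to 81.5%, 78.5% to 83.4% and 78.5% to 84.2% for assumed AUCs of 0.64, 0.69 and 0.73. Those gains of 2.2 to 5.7 points lie inside the range above. With no loss at all (164 per arm), the four prognostic scenarios gained 1.1 to 7.2 points, and the strongest reached 91.1%.

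**Step 4. Validity.** The simulated type I error of the chi-squared test was 4.4% to 5.3% against a nominal 5%.

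**Step 5. Chance imbalance.** Under simple randomisation, the standard deviation of the between-arm difference in a factor with 40% prevalence is √(2 × 0.4 × 0.6 / 148) = 5.7 points. A difference above 10 points (1.76 standard deviations) then occurs in about 8% of trials. At 164 per arm it is about 6%.

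**The case against.** The strongest reply is that nothing here is wrong. A chi-squared test is a legitimate primary test for a binary outcome. Under simple randomisation its error rate already allows for chance imbalance, as Step 4 shows. Collecting ARISCAT and naming subgroups does not commit the trial to adjustment. An adjusted or supporting model may sit in an analysis plan that is not shown. All of this stands, and it rules out calling the point an error or a contradiction. It does not remove the point, because the article itself names the unadjusted test as the method and a better one is available from data already planned.

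A reader might go further than the article allows in four ways:

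- *Randomisation is unstratified.* The article is silent on strata, and a condensed article may omit them. Only the absence of a description can be stated.
- *Adjustment removes chance imbalance.* It corrects only for the factors in the model.
- *The factors are strong predictors, so the gain is assured.* The article gives no odds ratio or AUC for either. Recording of surgical approach is itself inferred, from the planned procedure and the subgroup definition.
- *The lack of an effect estimate with a confidence interval is a fault.* That detail is commonly left to the analysis plan.

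**Conclusion.** The point holds as a free improvement. The stated test is valid but leaves unused two factors that should be known before randomisation after extubation.

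The gain is about 0 to 8 percentage points of power, set by prognostic strength that has to be assumed. If neither factor is prognostic, essentially nothing is lost. The gain was simulated only at the one-sided 0.025 critical value, where the starting power is about 79%. If alpha is two-sided 0.025 the start is about 70%, and the adjusted figure was not computed. The simulations used two binary factors or a single score, and not exactly the model proposed below, so the range is indicative.

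It would be tempting to offer adjustment as the remedy for the sample size. It is not: at 148 evaluable per arm even the strongest scenario reaches 87.9%, short of the stated 90%. The mismatch between 164 per arm and its own inputs is a larger and separate matter. So is the restriction of the final analysis, in the section on non-adherence and missing data {20c}, to participants with more than 75% adherence.

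**What to change.** Before any outcome data by arm are seen, replace the primary comparison with wording such as:

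> The primary analysis is a logistic regression of PPC by day 7 on treatment group, adjusted for ARISCAT score (continuous) and surgical approach (open or laparoscopic), both as known before randomisation. The result is reported as the marginal (standardised) risk difference and risk ratio with confidence intervals, tested at the alpha of the sample size section. An unadjusted chi-squared test is supportive.

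The marginal risk difference keeps the result on the scale of the 15-point difference used for planning. The sidedness of the 0.025 must be stated first, and the confidence level should match it. If strata were used in allocation, say so and include them in the model.

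The cost is a wording change and slightly more analysis work, with no extra patients. ARISCAT is already collected; surgical approach should be confirmed as a recorded item. The standardised risk difference with its interval may need software beyond SPSS 22, in which case the software sentence changes too.

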### Interim analyses {21b}

There are no interim analyses planned.

### Methods for additional analyses (e.g., subgroup analyses) {20b}

The treatment effect will be analysed according to the following pre-specified subgroups: (1) open surgery and laparoscopic surgery and (2) patients at high risk for PPCs (ARISCAT score ≥ 45).

### Methods in analysis to handle protocol non-adherence and any statistical methods to handle missing data {20c}

Final analysis will include all participants who had > 75% adherence to the protocol. Participants may withdraw from the trial at any time, then patient data collected up to that moment will be included in the analysis. Multiple imputation will be used to handle missing data if needed.

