#### Combination treatment group (Group A)

After extubation, patients will receive HFNC therapy for at least 48 h and respiratory training three times a day for at least 3 days.

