#### COT group (Group B)

COT would be continued for at least 48 h after extubation and may be continued or stopped after 48 h. Oxygen is transferred through a nasal catheter or a mask (with or without an oxygen storage bag or Venturi system). The oxygen flow is set to maintain SPO_2_ ≥ 95%. Patients can be considered for transfer out of ICU once oxygen flow is < 6L/min with SPO_2_ maintained at ≥ 95%.

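### The final analysis is restricted to participants with more than 75% adherence and no as-randomised analysis is named, so the primary comparison can be biased by an unknown amount in an unknown direction

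*Protocol article*

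**What the plan says.** Section {20c} sets the analysis population: "Final analysis will include all participants who had" more than 75% adherence to the protocol. The sentence is not limited to a per-protocol or sensitivity analysis, and no other analysis set appears in the article. Two further sentences follow. For participants who withdraw, "patient data collected up to that moment will be included in the analysis", and "Multiple imputation will be used to handle missing data if needed". How the 75% is counted is not stated for either arm.

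The arms carry different requirements. In Group A, "patients will receive HFNC therapy for at least 48 h and respiratory training three times a day for at least 3 days". In Group B, "Oxygen is transferred through a nasal catheter or a mask" for a minimum of 48 h, with no training component. Section {11b} lets investigators discontinue a participant for serious complications or for unsuitability to continue the Acapella device, which only Group A uses.

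The primary outcome (section {12}) is the incidence of PPCs within 7 days of surgery and includes acute respiratory failure. The Discussion places most postoperative respiratory failure in the first 72 h after surgery.

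**The concern.** Randomisation makes the groups comparable at the moment of allocation. A filter on something observed later keeps that comparability only if being filtered out is unrelated to prognosis, or if it acts alike in both arms. Neither can be assumed here.

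The period in which adherence is earned overlaps the period in which many primary events arise. A patient may fall below the threshold because a PPC is developing, and the event then leaves the analysis with the patient. Since the two arms have to adhere to different things for different lengths of time, the same event at the same hour can be kept in one arm and lost in the other.

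At stake are the type I error and the estimate for the primary endpoint. An unseen statistical analysis plan does not remove the problem. The article makes an explicit choice, and a plan based on intention to treat would contradict it.

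**Working it through.** **No plan figure to reproduce.** The article gives no non-adherence rate. The 164 per group is taken as stated; whether it follows from its own inputs is a separate question that does not affect this point.

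**Step 1: how one event can be treated differently.** Assume that adherence is counted against each arm's stated minimum, and that escalation stops the allocated treatment.
- Group A, counted by sessions: the minimum is 3 × 3 = 9. More than 75% means more than 6.75, so at least 7 sessions. A patient reintubated just after 48 h has had about 3 × 2 = 6, and 6/9 = 67%, so is excluded.
- Group B, counted by hours: 75% of 48 h is 36 h. A patient reintubated just after 48 h has 48/48 = 100% and is kept. One reintubated at 24 h has 24/48 = 50% and is excluded.

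Under this counting both arms can lose events, but over different windows. If Group A were counted by HFNC hours alone, the 48 h patient would be kept. The result depends on a definition that the article does not give.

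**Step 2: size under no true effect.**

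Inputs from section {14}: PPC risk 40% (applied to both arms), 164 per arm, α = 0.025. The article does not say whether α is one- or two-sided; one-sided is used here.

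Assumed inputs, not in the article: fraction excluded (e_A, e_B) and PPC risk r among the excluded, the same in both arms.

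Rate among those kept: p = (0.40 − e·r)/(1 − e).

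For e_A = 20%, e_B = 5%, r = 60%:
- A: (0.40 − 0.20 × 0.60)/0.80 = 0.28/0.80 = 35.0%
- B: (0.40 − 0.05 × 0.60)/0.95 = 0.37/0.95 = 38.9%
- Spurious benefit: 3.9 points, about a quarter of the 15-point target.

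Numbers kept: 164 × 0.80 = 131.2 and 164 × 0.95 = 155.8. The pooled rate is 0.371. Standard error under the null: √[0.371 × 0.629 × (1/131.2 + 1/155.8)] = 0.0573. Unpooled standard error: √[0.35 × 0.65/131.2 + 0.389 × 0.611/155.8] = 0.0571. The chance of a false benefit is 1 − Φ[(1.96 × 0.0573 − 0.0395)/0.0571] = 1 − Φ(1.27) = 10.1%.

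The same formula over a range (spurious benefit in points; chance of a false benefit):

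| Excluded A / B | r = 40% | r = 50% | r = 60% | r = 70% |
|---|---|---|---|---|
| 10% / 2% | 0; 2.5% | 0.9; 3.6% | 1.8; 5.1% | 2.7; 7.1% |
| 20% / 2% | 0; 2.5% | 2.3; 5.9% | 4.6; 12.3% | 6.9; 22.7% |
| 20% / 5% | 0; 2.5% | 2.0; 5.3% | 3.9; 10.1% | 5.9; 17.8% |
| 30% / 5% | 0; 2.5% | 3.8; 9.1% | 7.5; 24.5% | 11.3; 49.2% |

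**Step 3: the opposite direction.** Suppose the 20% excluded from A are mostly well patients who skip sessions, with 30% risk, and B stays as in the worked case. A becomes (0.40 − 0.20 × 0.30)/0.80 = 0.34/0.80 = 42.5% against 38.9%, a spurious harm of 3.6 points.

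**Step 4: the withdrawal sentence.** A participant who withdraws after day 3 may already exceed 75% of the intervention minimum, and the two sentences then agree. One who withdraws on day 1 will usually be below 75%. The first sentence drops that participant and the second keeps the data.

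**The case against.** The best defence is that the article does not show how large the problem is, or which way it runs. That stands. The protocol requirements support a heavier burden in Group A but not a measured difference in adherence. Section {11a} allows flow to be reduced for discomfort, so that tolerance problem need not count as non-adherence. Section {11c} also deals with telephone calls and later follow-up under adherence, so the 75% may not refer to HFNC hours and training sessions alone.

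A reader might infer four stronger claims that the documents do not support:
- **The bias favours the combination.** This is plausible if deteriorating patients miss HFNC or sessions, but Step 3 shows that the reverse is also possible.
- **Group B loses almost no events.** A Group B patient escalated to NIV or reintubated within the first 48 h can also fall below the threshold.
- **The withdrawal sentence contradicts the rule.** It conflicts only for early withdrawals.
- **The adherence exclusions come on top of the 10% loss allowance.** Section {14} does not say whether they fall inside or outside it.

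None of this rescues the rule. It remains the only stated analysis set, it is defined after randomisation, and its lack of definition adds to the problem.

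**Conclusion.** The rule is wrong as written and must be changed. That conclusion rests only on the text: the population is selected on a post-randomisation variable that overlaps in time with the primary outcome and means different things in the two arms.

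The numbers are illustrative. They assume no true effect, a one-sided 0.025 test, exclusion of 10–30% in A and 2–5% in B, and the same raised PPC risk of 50–70% among the excluded in both arms. Under those assumptions the false-benefit chance is about 3.6% to 49%. The risk among the excluded is a highly influential input: at 40% there is no bias.

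**What to change.** Replace the first sentence of section {20c}, and bring the withdrawal and imputation sentences into line with it:

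> The primary analysis includes all randomised participants in the group to which they were assigned, regardless of adherence, using PPC data to day 7 collected also after discontinuation of the intervention where consent allows, with multiple imputation for missing PPC status. An analysis of participants with more than 75% adherence, defined for each arm, is a sensitivity analysis.

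The wording costs little, and the definition of adherence should be fixed before the data are analysed. The estimate may be smaller than in adherers. Outcome collection to day 7 has to continue for participants discontinued under section {11b}. Randomisation began in November 2021, so some of those data may already be missing and need imputation.
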